## Recruitment {15}

The inclusion age range of subjects has been set at 45–75 which reflects the subject age demographic and time of disease presentation with consideration for surgical intervention for prostate cancer at the University of Rochester (URMC) Cancer Center.

### Assignment of interventions: allocation

#### Sequence generation {16a}

Participants are enrolled in this study in a series of four blocks to ensure that there is not a significant skewing of participants receiving the study drug or placebo at any given point. Each block is a series of randomization numbers and then randomly assigned to an active or placebo treatment course. The patient is enrolled during the surgery after the nerve-sparing portion of the surgery, if a sufficient bilateral NSRP was able to be performed. At this time, the surgical team contacts the pharmacy, and the participant is then assigned a computer-generated randomization number. Each randomization number is associated with the date, study subject initials, the study assigned subject number, whether the act of drug or placebo was given, the lot number of the product, the expiration date of the product, and the initials of the pharmacist.

#### Concealment mechanism {16b}

Each prescription is filled with labels that state the drug as “Dalfampridine 10 mg/placebo study drug.” All capsules are packaged by the University Pharmacy using identical size and color capsules. A sealed study subject-specific envelope is created for each subject enrolled that contains an index card that details whether that subject received active or placebo capsules. If the blinded staff is required to unblind themselves, the envelope is opened and the person, date/time of unblinding, and the reason for unblinding are documented.

#### Implementation {16c}

The Investigational Drug Service (IDS) at the University of Rochester will randomize subjects prior to scheduled nerve-sparing radical retro-pubic prostatectomy surgery in a 1:1 ration to the treatment or placebo group.

### Assignment of interventions: blinding

#### Who will be blinded {17a}

Both the subject and the provider will be blinded to group assignment to avoid selection bias. The Investigational Drug Service (IDS) will randomize subjects and dispense study medication and therefore, remain unblinded.

#### Procedure for unblinding if needed {17b}

In the event of a medical emergency, the principal investigator and/or DSMC may decide to disclose drug assignment. The Investigational Drug Service will provide a sealed envelope with the subject’s drug assignment to the blinded study team. If unblinded, the subject will receive no further study drug doses and will be withdrawn from the study.

### Data collection and management

#### Plans for assessment and collection of outcomes {18a}

Standard of care laboratory tests include urinalysis, CBC, and BMP, which will be completed pre-operatively.

Three questionnaires will be administered pre-operatively and post-op week 3. Completion of the three questionnaires will continue every other week from post-op week 4 to month 6 and then again at months 9 and 12. Subjects will complete the questionnaires throughout the study by entering their responses directly into a REDCap database, during an in-person visit, and/or via telephone with the study personnel. REDCap is a secure research data capture program supported by the University of Rochester.

At 3 months post-op, and for the duration of the study, subjects will be offered treatment for erectile dysfunction. Treatment options will be guided by the results from the IIEF-5 questionnaire and algorithm for erectile dysfunction.

As an internal control, subjects will be asked to complete an additional questionnaire at week 8 to assess whether they believe they received the active drug or placebo.

#### Plans to promote participant retention and complete follow-up {18b}

All patients included in the study are on an intention-to-treat basis. Patients who do not complete the full study will have their data included for statistical use. The final outcomes are computed based on these accepted statistical protocols and reviewed by a qualified statistician.

#### Data management {19}

Study data will be collected and maintained in the University of Rochester’s REDCap system. REDCap servers are secured in a local data center at the University of Rochester, and all web-based information transmission is encrypted.

#### Confidentiality {27}

Data will be stored on password-protected and encrypted computers using a secure drive at the University of Rochester Medical Center. Access will be restricted to the investigators, the study coordinator, and any agency legally empowered to demand access to the data.

Subject data is coded using a unique number, and all identifying information (i.e., name, address, phone number) will be stored separately via a study master key linked to the code. The master key will be destroyed by the investigative team after the study is completed and all data has been analyzed.

The results of this study will be published at scientific meetings and in publications without disclosure of subject identity.

#### Plans for collection, laboratory evaluation, and storage of biological specimens for genetic or molecular analysis in this trial/future use {33}

Subject information collected as part of this study will not be distributed or used for future research studies.

## Statistical methods

### Statistical methods for primary and secondary outcomes {20a}

#### Planned statistical analysis

The data analysis will be based on the principle of intention to treat.

(1) Descriptive statistics:

Descriptive statistics for all covariates and outcomes will be reported. For categorical variables, the frequency will be reported. Pearson’s chi-square test or Fisher’s exact test will be used to compare the difference between the two groups. For continuous variables, the mean, standard deviation, and median will be calculated. Two-sample *t*-test (for normally distributed data) or Wilcoxon rank test will be used to compare them in the two groups.

(2) Analysis of outcomes:

(2.1) Analysis of the primary outcome.Pearson’s chi-square test will be used to compare the rates of returning to the baseline ability by the end of the follow-up.Since this is a longitudinal study, we anticipate some patients will drop out during the follow-up. We assume that the dropout is monotone and random, which means that once they drop out, they will not come back to the study, and the dropout only depends on the information up to the point of dropout. We will model the probability of dropout by logistic regression. The weighted generalized estimation equation (GEE) (with logit link) will be used to study the treatment effects on the returning to the baseline ability at each visit after adjusting the effects of some baseline demographic and clinical factors [14, 15].

(2.2) Analysis of secondary outcomes:Return to baseline erectile function as measured by the IIEF-5: The same method as in the primary outcome will be used.A more rapid recovery (time frame) of subject-reported erectile function measured by the Abridged International Index of Erectile Function (IIEF-5): The Kaplan–Meier estimator will be used to estimate the distribution function of the time of recovery. The log-rank test will be used to compare the distributions of the two groups.Improved recovery of baseline subject reported continence using the Michigan Incontinence Symptom Index (M-ISI) in the intervention group: The same method as in the primary outcome will be used.Decreased use of medications and devices for erectile dysfunction measured by the Attempted Sexual Intercourse and Use of Erectile Aids questionnaire: The weighted GEE (with identity link) will be used to study the effects of treatment on the use of medications and devices at each visit after adjusting the effects of some baseline demographic and clinical factors [14].

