### Outcomes {12}

#### Primary outcome

The primary outcome is return to baseline confidence in the ability to achieve and maintain erection as measured by item 1 of the Abridged International Index of Erectile Function (IIEF-5) by 12 weeks after surgery.

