## Sample size {14}

The primary outcome is return to baseline ability to achieve and maintain erection as measured by Item of the Abridged International Index of Erectile Function (IIEF-5) by 12 weeks after surgery. Suppose at the conclusion of the follow-up period, the rates of returning to the baseline ability in the treatment and control groups are 70% and 30%, respectively. Pearson’s chi-square test indicates that a sample size of 56 (with 28 individuals in each group) achieves 90% power to detect the intended difference of 40% (at a significance level of 0.05). Accounting for an estimated dropout rate of 30%, we plan to recruit 40 subjects in each group.

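### The named outcome analyses of IIEF-5 total and M-ISI use only a yes/no return to baseline; adding a baseline-adjusted comparison of the scores would be a cheap improvement

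*Protocol article*

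**What the plan says.** Under Planned statistical analysis, item (2.2), the two scale-based recovery outcomes borrow the primary method: "Return to baseline erectile function as measured by the IIEF-5: The same method as in the primary outcome will be used", and "Improved recovery of baseline subject reported continence using the Michigan Incontinence Symptom Index (M-ISI) in the intervention group: The same method as in the primary" outcome method is used.

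Item (2.1) defines that method. Its first part is "Pearson’s chi-square test will be used to compare the rates of returning to the baseline ability by the end of the follow-up". Its second part is a weighted GEE with logit link at each visit, adjusted for some baseline factors. Both parts take a yes/no response.

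Item (2.2) also gives the IIEF-5 a Kaplan–Meier and log-rank analysis of time to recovery. The M-ISI has no such analysis. Use of erectile aids is to be analysed by weighted GEE with identity link.

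Item (1), on descriptive statistics, covers covariates and outcomes together and provides a two-sample t-test or Wilcoxon test for continuous variables.

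The primary outcome is return to baseline "as measured by item 1 of the Abridged International Index of Erectile Function (IIEF-5) by 12 weeks after surgery". The sample size section assumes that "the rates of returning to the baseline ability in the treatment and control groups are 70% and 30%, respectively". It states this for the primary outcome only.

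**The concern.** The IIEF-5 total and the M-ISI are multi-point scales, recorded before surgery and repeatedly afterwards. Once each is reduced to back at baseline or not, a man one point short counts the same as a man with no recovery, and one point of response noise can move a man across the line.

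The article's own background describes recovery that runs over weeks to years, and its discussion says that significant erectile dysfunction is common three months after surgery. At week 12 some men may therefore be partly recovered, and the planned recovery analyses count them as failures. If 4AP gives a partial early gain, a trial of this size could miss it on these two outcomes or estimate it poorly.

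**Working it through.** **Inputs from the protocol article.** Sample size section: 70% v 30% for item 1 of the IIEF-5, 28 evaluable per group, significance level 0.05 (taken as two-sided), 30% dropout, 40 recruited per group. Eligibility: IIEF-5 of at least 17 at screening.

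**Assumed, because the documents are silent.** Any effect, SD or distribution for the IIEF-5 total or M-ISI; the use of 70% v 30% for them; the smaller effects of 60%, 55% and 40% v 30%.

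**Step 1: the plan's own figure.** With unpooled variance, n = (0.21 + 0.21)(1.96 + 1.2816)² / 0.40² = 27.6, so 28 per group, as stated. Dropout: 28 / (1 − 0.30) = 40, as stated. At 28 per group the pooled formula gives 87.0% power, and exact enumeration of the uncorrected chi-square gives 86.1%. The exact figure is the benchmark below.

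**Step 2: the same effect on a normal score.** If the score is normal with equal variance and is cut at baseline, rates p1 and p0 imply a shift d = z(p1) − z(p0) in SD units. For 70% v 30%, d = 0.524 + 0.524 = 1.049. The t-test has noncentrality d√(n/2) on 2n − 2 degrees of freedom; at n = 28 this is 1.049 × 3.742 = 3.92 on 54.

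| Per arm | Rates | d | Chi-square (yes/no) | t-test (score) | Loss, points |
|---|---|---|---|---|---|
| 28 | 70% v 30% | 1.049 | 86.1% | 97.1% | 11 |
| 28 | 60% v 30% | 0.778 | 61.3% | 81.5% | 20 |
| 28 | 55% v 30% | 0.650 | 46.5% | 66.6% | 20 |
| 28 | 40% v 30% | 0.271 | 12.4% | 16.9% | 4.5 |
| 40 | 70% v 30% | 1.049 | 96.4% | 99.6% | 3 |
| 40 | 60% v 30% | 0.778 | 79.6% | 93.0% | 13 |
| 40 | 55% v 30% | 0.650 | 64.0% | 81.9% | 18 |

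**Step 3: a bounded score (simulation, 4,000 runs, 28 per arm).** Assumed: baseline about 21.5 (SD 2.3) limited to 17–25, ceiling 25, change SD 6. The score analyses are Wilcoxon on change and baseline-adjusted regression.
- 70% v 30%: chi-square 86.0%, Wilcoxon 93.1%, regression 94.7%; loss 7–9 points.
- 55% v 30%: chi-square 46.9%, Wilcoxon 59.3%, regression 60.9%; loss 12–14 points.

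**Step 4: all-or-none recovery (same simulation size).** Assumed: recovered men sit at or just above baseline, and the others are spread over scores 5–16 whatever their arm.
- 70% v 30%: chi-square 85.9%, Wilcoxon 75.7%, regression 79.5%.
- 55% v 30%: chi-square 46.8%, Wilcoxon 35.8%, regression 39.6%.

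Here the yes/no analysis is the stronger one.

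**The case against.** **A score comparison may already be planned.** The descriptive paragraph covers outcomes and provides a t-test or Wilcoxon test for continuous variables. It can be read as including both scores, so a reader who concluded that no score comparison is planned would go too far. What remains is that the paragraph names neither scale nor any visit, has no baseline adjustment or dropout weighting, and stands apart from the outcome analyses.

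**Chi-square is not the whole analysis.** The weighted GEE uses repeated visits, and the IIEF-5 log-rank test uses timing. The figures above compare single-time-point tests and so probably overstate the loss, at least for the IIEF-5. This stands, although every one of these analyses still treats recovery as an event, and the M-ISI has no time-to-recovery test.

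**The size depends on the model.** It does. A reader might take 11 or 20 points as the cost in this trial at the plan's own effect. The documents do not support that: 70% v 30% belongs to item 1, nothing is stated for the IIEF-5 total or M-ISI, and the sign changes under all-or-none recovery. The article's account of slow and variable recovery makes that pattern less likely but does not exclude it.

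**Return to baseline is the declared question.** The trial design and outcome sections both say so, and a mean score difference answers a somewhat different one. This stands against replacing or demoting the declared outcomes. It does not stand against adding a score analysis beside them.

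**The article is a condensed document.** A fuller plan may add a score model. But the yes/no method for these outcomes is stated here as a choice, not left open.

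**Conclusion.** The point holds as a cheap improvement, not as an error in the design. The named outcome analyses of IIEF-5 total and M-ISI rest on return to baseline alone, and no baseline-adjusted analysis of either score is specified.

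Under an equal-variance normal score with 28 evaluable per arm and a single-time-point test, the cut costs about 11 points of power at 70% v 30% and about 20 at 55–60% v 30%. With 40 per arm the loss is about 3 points at 70% v 30% and about 18 at 55% v 30%. It shrinks for a bounded score, and at 70% v 30% the score analysis falls 6–10 points below chi-square if recovery is all-or-none. These are illustrations under stated assumptions.

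The uncertainty about the recovery pattern is itself the reason to report both analyses. Nothing here calls for a change to the primary outcome or its test.

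**What to change.** Keep return to baseline as the declared primary and secondary outcomes, with the analyses now planned. Before unblinding, prespecify one further secondary analysis per scale: a baseline-adjusted comparison of the IIEF-5 total and of the M-ISI score at week 12, fitted by the identity-link weighted GEE already planned for aid use and reported beside the proportions back to baseline. If the full protocol or SAP already contains this, a cross-reference is enough.

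No new data are needed, since the questionnaires are already scheduled. The cost is a little more programming, one more secondary analysis per scale, and a mean difference that is less direct to explain than back to baseline.

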#### Criteria for discontinuing or modifying allocated interventions {11b}

Subjects will be withdrawn from the study for the following:If the subject is unable or unwilling to take the study drug.Subjects planned for a NSRP but who did not receive a nerve-sparing procedure intraoperatively.Subjects who have experienced a seizure while taking the study medication.Subjects who take ED treatments within the 3-month period after surgery.Any subject with an eGFR less than 60 mL/min/1.73 m^2^ while on the study, if clinically indicated, will have a repeat serum BUN and creatinine within 2–3 days, and if eGFR is still less than 60 mL/min/1.73 m^2^, they will be promptly withdrawn from the study.In subjects who incidentally demonstrate a decrease in eGFR > 30 mL/min on study, but still maintain an eGFR ≥ 60 mL/min, we will obtain repeat BUN and creatinine within 2–3 days, and if eGFR based on repeat labs is < 60 mL/min, they will be promptly withdrawn from the study.Subjects with final surgical pathology showing pT3 disease, positive nodes, or positive surgical margins who require adjuvant treatment (such as androgen deprivation therapy or radiation) as adjuvant treatments can worsen ED and UI after NSRP.The Data Safety Monitoring Committee (DSMC) and/or principal investigator may withdraw any subject at increased risk using the best medical opinion based on reported AEs/SAEs.

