#### Methods in analysis to handle protocol non-adherence and any statistical methods to handle missing data {20c}

This is a typical longitudinal study. Missing data is almost unavoidable. Although we can never test the missing mechanism assumption based on the observed data, the data missing at random (MAR) is usually a reasonable assumption. In the data analysis, we will make this assumption. The current semiparametric method can only handle the missing data with a monotone missing pattern which means that if the patient misses one scheduled visit, then they will miss all visits thereafter. We will artificially truncate data after the first missed appointment if this occurs.

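### Time to recovery is analysed by unweighted Kaplan–Meier and log-rank, which need a stronger dropout assumption than the plan itself makes

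*Protocol article*

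**What the plan says.** All references are to the protocol article.

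- **Time to recovery** (Planned statistical analysis, secondary outcomes): "The Kaplan–Meier estimator will be used to estimate the distribution function of the time of recovery", and "The log-rank test will be used to compare the distributions of the two groups". No weights, covariates or censoring rule are given for this outcome.
- **Dropout assumption** (same section, primary outcome): dropout is taken to be monotone and random, meaning that "the dropout only depends on the information up to the point of dropout". The plan continues "We will model the probability of dropout by logistic regression" and puts that model to use in a weighted GEE. Section {20c} repeats the missing-at-random assumption and adds "We will artificially truncate data after the first missed appointment if this occurs".
- **Withdrawals** (section {11b}): the list includes "Subjects who take ED treatments within the 3-month period after surgery" and men whose pathology leads to adjuvant treatment, the stated reason being "as adjuvant treatments can worsen ED and UI after NSRP".
- **Expected loss** (Sample size {14}): "Accounting for an estimated dropout rate of 30" per cent, the plan recruits 40 men per arm.

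**The concern.** A Kaplan–Meier curve lets a censored man drop out of the risk set and, in effect, gives him the recovery hazard of the men who stay. That is right only if, among men not yet recovered, leaving carries no information about later recovery. Missingness at random given observed history is weaker: a man with a low IIEF-5 score at week 6 may be more likely to leave and less likely to recover, and the assumption still holds. The plan allows for this in the GEE by weighting, but not in the one analysis that treats recovery as a time.

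Two withdrawal rules make such dependence plausible. Men who turn to ED treatment early are likely to be those not recovering, and the protocol itself says that adjuvant treatment can worsen function. If these men are censored, the recovery curves would be too high. If reasons for leaving differ between arms, the log-rank comparison would be distorted too. The trial's hypothesis is that the drug speeds recovery, so this outcome carries weight although it is secondary.

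**Working it through.** **1. The plan's own figures.** With 70% v 30%, two-sided 0.05 and 90% power, the unpooled formula gives n = (1.960 + 1.282)² × (0.7×0.3 + 0.3×0.7) / 0.4² = 27.6, so 28 per arm; 28 / 0.70 = 40. Both stated sizes reproduce. Expected dropouts are 0.30 × 80 = 24.

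**2. Model.** The documents give no figure for time to recovery, so I assume:
- true recovery by week 12 of 70% and 30% (section {14}, where the figures belong to IIEF-5 item 1);
- visits at weeks 3, 4, 6, 8, 10 and 12;
- three states (far from baseline, near it, recovered), with all men starting far and moving up one state per visit with probability p.

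Recovery by the sixth visit is 1 − (1−p)⁶ − 6p(1−p)⁵, so p = 0.360 gives 70% and p = 0.182 gives 30%. After each of the first five visits, unrecovered men leave with a probability that depends on their state, scaled so that 30% of the arm leaves in total.

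**3. Limit of the estimator.** With F and N the proportions far and near among men still followed at a visit, the recovery hazard is N·p / (F + N), and the curve is 1 − Π(1 − hazard) over visits.

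| Dropout ratio, far : near | True 70% | True 30% | Difference |
|---|---|---|---|
| 1 (unrelated to state) | 70.0% | 30.0% | 40.0 |
| 2 | 72.3% | 31.7% | 40.6 |
| 4 | 74.2% | 32.8% | 41.4 |
| only far men leave | 77.3% | 34.5% | 42.8 |

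The overstatement is therefore about 2 to 7 points per arm. The SE of one arm's curve at week 12 is about 8 to 9 points with 40 men.

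**4. A different model.** With a normally distributed prognostic factor driving both recovery and dropout, 30% becomes 33–36% and 70% becomes 74–80%, depending on the strength of dependence. That is about 3 to 10 points, and again zero when dropout is unrelated to prognosis.

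**5. Comparison of arms.**
- *Same pattern in both arms:* at ratios 2 and 4 the difference moves by 0.6 and 1.4 points (2.8 if only far men leave). Simulated log-rank error under the null stays at about 5%.
- *4:1 pattern in one arm only:* 74.2 − 30.0 = 44.2, or 70.0 − 32.8 = 37.2, instead of 40, with SE about 12. Under a true 50% v 50%, upper-tail error is about 4.7 to 4.9% instead of 2.5%.
- *Second model, dropout differing by arm:* two-sided rejection under the null is about 7 to 8%.

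**6. Effect of weighting.** Each man still at risk at visit k gets weight Π 1/(1 − d_j) over earlier visits j, where d_j is his modelled dropout probability given his history. In the three-state model this returns differences of about 40 and 0 points. Weights estimated from 40 men per arm also remove the bias, with almost the same SE (0.12 to 0.13).

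**The case against.** The case for leaving the plan alone has real content.

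- **Dependence is allowed, not asserted.** A reader might infer that the curves are biased upward. The document does not support that: the dropout assumption limits what dropout may depend on and does not say that scores matter. Withdrawals for seizure, renal function or unwillingness to take the drug need not relate to recovery. This stands, and the bias is conditional.
- **No censoring rule is written.** A reader might infer that withdrawn men can only be censored. Intention to treat is stated, and non-completers' data are to be included, so they could instead be counted as not recovered. Censoring is the default reading and no more.
- **The assumptions are not incompatible.** Independent censoring is stronger than missingness at random and can hold together with it. The primary outcome also pairs a plain chi-square test with the weighted GEE.
- **A weighted analysis exists.** Return to baseline IIEF-5 gets the primary outcome's methods, including a weighted GEE at each visit. This stands: early recovery is already examined with weighting, though not as a time.
- **The comparison is robust to a shared pattern.** This also stands. Harm to the test needs a pattern that differs by arm, in a double-blind trial, and even then the shift is about 0.3 SE.
- **Weighting has limits.** Every man who meets a withdrawal rule leaves, so weights repair only what recorded scores predict.

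It might also be said that such detail belongs in an analysis plan not shown. But the article names the estimator and the test, and states a dropout assumption too weak to justify them. That is a method fixed, not a detail left open.

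**Conclusion.** The point holds as a mismatch between a named method and the plan's stated dropout assumption, for one secondary outcome. If early leavers are censored and poorer-scoring men leave more often, recovery is overstated by about 2 to 7 points per arm in the three-state model, and by up to about 10 in the other. If dropout is unrelated to prognosis there is no bias. The documents cannot fix the size, because they do not say what share of departures is outcome-related.

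The test is at material risk only if dropout patterns differ by arm: a shift of about 3 to 4 points against an SE of about 12, in a direction that cannot be known in advance. The primary chi-square test, the sample size and the weighted GEE of IIEF-5 return are unaffected. This is an inexpensive improvement worth making before analysis, not a flaw that invalidates the trial.

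**What to change.** In the secondary-outcome analysis, replace the plain estimator and test with Kaplan–Meier curves and a log-rank test weighted by the inverse probability of remaining (or a weighted Cox model with robust SE). Take the weights from the logistic dropout model already planned for the GEE, with earlier IIEF-5 scores among its predictors, and stabilise or truncate them. Report the unweighted log-rank test alongside.

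State how men who leave enter this analysis. Add a sensitivity analysis that keeps men withdrawn for early ED treatment or adjuvant therapy in the risk set as not recovered, since weighting cannot recover what their recorded scores do not predict.

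The cost is a few sentences and modest programming. The drawback is somewhat more variable weights, because the dropout model would rest on about 24 departures.

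### Time to IIEF-5 recovery is the only listed efficacy outcome without a baseline-adjusted analysis; the log-rank is valid but may give up some power

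*Protocol article*

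**What the plan says.** Under Planned statistical analysis, the protocol article gives these methods for the efficacy outcomes:

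- **Primary outcome (IIEF-5 item 1).** First an unadjusted comparison: a "chi-square test will be used to compare the rates of returning to the baseline ability by the end of the follow-up". Then a weighted GEE with logit link for "treatment effects on the returning to the baseline ability at each visit after adjusting the effects of some baseline demographic and clinical factors".
- **Return to baseline IIEF-5, and M-ISI continence.** For each, "The same method as in the primary outcome will be used", so each has both the chi-square and the adjusted GEE.
- **Erectile aids.** A weighted GEE with identity link for "use of medications and devices at each visit after adjusting the effects of some baseline demographic and clinical factors".
- **Speed of recovery.** The item reads "A more rapid recovery (time frame) of subject-reported erectile function", measured by the IIEF-5. It gets Kaplan–Meier curves, and then "The log-rank test will be used to compare the distributions of the two groups". No stratification, covariate or hazard ratio is mentioned.

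Eligibility criteria {10} admits men aged 45–75 with a screening IIEF-5 of at least 17. The IIEF-5 is also completed before surgery (Research visit 1). Age and baseline IIEF-5 are therefore already in the database for every man.

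**The concern.** The trial's hypothesis is about speed (Objectives {7}, Trial design {8}), and this is the one listed analysis of a time to recovery. It is also the one listed efficacy outcome with no adjusted version, and the article gives no reason for treating it differently.

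When recovery times depend on baseline characteristics, a proportional-hazards comparison that ignores them estimates a hazard ratio nearer to 1 and has less power than one that includes them. With 28 evaluable men per group (40 recruited), the trial has little power to spare on a secondary outcome. A log-rank reported alone also yields a p-value without an effect size or an interval.

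**Working it through.** **1. The plan's own figure.** Sample size {14} assumes 70% v 30% at 90% power and a 0.05 level, taken here as two-sided. With unpooled variance:

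n = (1.960 + 1.282)² × (0.70×0.30 + 0.30×0.70) / 0.40² = 27.58, so 28 per group. Then 28 / (1 − 0.30) = 40 per group.

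This reproduces the stated figures. It concerns the primary outcome only; no power is claimed for the log-rank.

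**2. Planning effect on the time scale.** Assume that the item 1 rates carry over to IIEF-5 recovery and that hazards are proportional. Then HR = ln(0.30)/ln(0.70) = 3.38, where a value above 1 means faster recovery. At 28 per group the expected events by week 12 are 28 × (0.70 + 0.30) = 28. Schoenfeld power is Φ(½√28 × ln 3.38 − 1.96) = 89.6%. At 40 per group (40 events) it is 97.0%.

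**3. Log-rank against adjusted Cox at the protocol's control rate.** Setup: exponential recovery times rounded up to the next planned questionnaire; 30% of controls recovered by week 12; no dropout; one standard-normal covariate with log-hazard *b* per SD. The Cox model used Efron ties and a likelihood-ratio test. There were 1,000 trials per cell, so the standard error is at most √(0.5×0.5/1000) = 1.6 points. The article gives no value for *b*, so a range is shown.

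| Setting | *b* = 0 | *b* = 0.25 | *b* = 0.5 | *b* = 1.0 |
|---|---|---|---|---|
| HR 3.38, 28/group, to week 12 | 88.7 v 88.3% | 86.6 v 87.0% | 83.3 v 87.9% | 67.0 v 84.8% |
| HR 3.38, 40/group, to week 52 | 100 v 100% | 99.5 v 99.8% | 99.1 v 99.9% | 90.9 v 99.4% |
| HR 2.0, 28/group, to week 12 | 37.3 v 37.5% | 36.5 v 38.1% | 35.4 v 36.6% | 26.0 v 34.4% |
| HR 2.0, 40/group, to week 52 | 83.0 v 81.6% | 77.8 v 79.9% | 69.2 v 80.4% | 47.6 v 72.8% |

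(Each cell: log-rank v adjusted Cox.)

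**4. Smaller effects with more events.** Setup: 28 per group; visits at weeks 3, 4, 6, 8, 10 and 12; about half of controls recovered by week 12 (assumed); two covariates forming a prognostic index. Results of two independent runs, log-rank v adjusted Cox:

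| True HR | No covariate effect | 0.5 per SD of index | 0.8 per SD of index |
|---|---|---|---|
| 2.0 | 51 v 51%; 53 v 50% | 41 v 49%; 45 v 51% | 33 v 45%; 37 v 48% |
| 2.5 | 77 v 75% (one run) | 69 v 75%; 69 v 75% | 55 v 71%; 54 v 69% |

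The gaps at 0.5–0.8 per SD run from 6 to 16 points.

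**5. Error rate.** With no treatment effect, the runs in step 3 rejected in 4.2–6.3% of trials (log-rank) and 4.0–6.2% (adjusted Cox), with a simulation error of about 0.7 points. Adjustment did not inflate the type I error.

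**The case against.** The strongest reply is that nothing here is wrong. A log-rank test after 1:1 randomization is standard, and its type I error does not need proportional hazards. A different method for a time-to-event outcome is not a contradiction, and an unseen analysis plan may add a Cox model. The first two points stand: this is neither bias nor an internal conflict. On the third, the article does fix the test for this item, and in the same section it specifies adjustment for the neighbouring outcomes. The choice can therefore be commented on as written.

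Four stronger readings are tempting, and the article does not support them:

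- *This is the only test of the trial's question.* It is one of four secondary outcomes. The primary outcome is itself early recovery, by 12 weeks, and an adjusted visit-by-visit GEE of IIEF-5 return to baseline is already planned.
- *It is the only analysis left unadjusted.* The chi-square listed first for the primary outcome, on which the sample size rests, is unadjusted too. The difference is that the primary outcome also has an adjusted companion.
- *A target equal to the man's own baseline makes baseline prognostic.* A higher score may mean better function but also sets a higher bar, and entry at 17 or more narrows the range. This item does not itself define recovery as return to the man's own baseline.
- *Power is lost for nothing.* The loss is conditional on a prognostic strength that the article does not give. Adjustment also has costs: a proportional-hazards assumption, a conditional rather than marginal hazard ratio, and up to about 3 points of power if the covariates are uninformative (53 v 50% above).

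**Conclusion.** The point holds as one of efficiency and consistency on a secondary outcome. The plan's log-rank is valid.

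The size depends on three unknowns: how prognostic the covariates are, the true effect, and how many men recover.

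- At hazard ratios of 2–2.5 and 0.5–0.8 log-hazard per SD, the unadjusted test gives up roughly 5–15 points. This needs a reasonable number of events, such as half of controls recovered by week 12 or follow-up to week 52. With 30% of controls recovered, 28 per group, follow-up to week 12 and HR 2, the gain at 0.5 per SD is only about 1 point (35.4 v 36.6%).
- At the planning effect (HR about 3.4), the loss is about 0–5 points for covariate effects up to 0.5 per SD. It becomes large only for a strong covariate (67.0 v 84.8% at 1.0 per SD).
- With no covariate effect, nothing is lost by leaving the test unadjusted.

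All of these figures assume proportional hazards and exponential recovery times; step 3 also assumes no dropout. The trade-off favours adjustment: a possible cost of about 1–3 points against a larger possible gain, at an unchanged error rate. It is worth making, but the validity of the trial does not depend on it.

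**What to change.** In Planned statistical analysis, before unblinding, name as the main test of time to IIEF-5 recovery a Cox model, or its discrete-time complementary log-log form, with treatment, age and baseline IIEF-5. Report the hazard ratio with its 95% confidence interval. Keep the Kaplan–Meier curves for display and the log-rank as a supporting test.

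Recovery is seen only at questionnaire dates, so many times will be tied. Use the discrete-time form or Efron's method; in a check on the step 4 setup, Breslow's approximation gave back essentially all of the gain from adjustment. State how proportional hazards will be examined, and that the hazard ratio is conditional on the covariates.

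A log-rank stratified by baseline IIEF-5 is a weaker alternative. At HR 2.5 and 0.8 per SD it reached 58% power, against 54% for the plain log-rank and 69% for the adjusted Cox model.

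The change is a sentence or two of text. Both covariates are already collected, and neither the visits nor the sample size changes.
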